### Participant eligibility

#### Inclusion criteria

The inclusion criteria were established after an exhaustive review of the scientific literature and consensus among all participating psychiatric and clinical psychologists. Study subjects are aged ≥18 years, has had a previous major depressive episode within the last five years and are in a stage of total or partial remission within the last six months, based on DSM-5 criteria. One participant who has undergone a single depression episode is included for every three participants who had undergone two or more episodes.

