### Patient recruitment

In a first phase of the selection process, we extract names of potential participants from the clinical records of the hospitals or health centers who are willing to collaborate with the study. Next, the participating psychologists and psychiatrists review the clinical records individually to identify the subjects that comply with the inclusion criteria. The potential participants are contacted by phone or during a clinical visit. When a candidate agrees to participate, a face-to-face interview with the specialist is carried out to exclude participants who do not meet the criteria. Besides the semi-structured clinical interview (Spanish SCID-I) [15], participants also self-complete the Beck Depression Inventory to assess depressive symptoms [16]. Information about the participant is completed with questions from the eligibility questionnaire, such as medical conditions or problems related with the adherence to the Mediterranean diet. During the first visit, participants receive a brief explanation of the study, are informed that are going to be given extra-virgin olive oil for the duration of the trial at no cost, and a signed informed consent is obtained. All study participants are asked to provide blood samples (previous appointment with the hospital) and a subgroup of participants is instructed to also provide urine samples (recruitment centers: Vitoria, Pamplona) and stool samples (recruitment center: Vitoria).

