### Sample size and data analyses

The original sample size calculation indicated that 250 people per group were required (assuming an attrition of 5%) to provide a statistical power of 80% for detecting a relative risk reduction of 30% in the Mediterranean diet group versus the control group for a two-year follow-up period. The assumed recurrence rate was 50% for the control group and 35% for the group assigned to the Mediterranean diet. The relative risk reduction of 30% was slightly lower than the observed in the SUN cohort study. In this latter study, we found a 40% risk reduction of depression comparing extreme quintiles of adherence to the Mediterranean Diet Score [23] and the observed among diabetic participants of the PREDIMED trial after three years of intervention with the Mediterranean diet supplemented with nuts [24].

A researcher blinded to the conditions of the intervention will carry out the analysis of the data. Intention-to-treat analysis will be done. For each participant we will compute person-years of follow-up from the study inclusion date to the date of recurrence of the depression or study termination, whichever comes first.

Log Rank analysis will be used to assess the effect of the intervention on the risk of depression recurrence. If distribution differences of baseline characteristics are detected, the Cox proportional-hazards regression models will be used to check by recruitment center, age group and sex, and adjusting for possible confounding factors (educational level, marital status, prevalence of diseases, body mass index, tobacco use, leisure-time physical activity, alcohol intake, total energy intake, type, dose and use of antidepressants, psychotherapy, presence, number, and time since last of depressive symptoms/episodes, and family history of mental disorders). Hazard ratios (HR) and 95% confidence intervals (CI) will be calculated considering the control group as reference.

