We will also carry out a protocol analysis [25]. Categories of adherence to the Mediterranean diet will be defined using information from the FFQ and MEDAS, and Cox regression models will be fitted. Marginal structural models (inverse probability of exposure-weighted estimators) will be fitted to exposure measures that vary over time [26]. Finally, to examine quantitative variables such adherence to the Mediterranean diet scorings [27], other analysis will be explored, e.g., smoothing splines and regression analysis based on fractional polynomials [28, 29].

Changes in residual depressive symptoms, quality of life or biochemical parameters were evaluated through Generalized Estimating Equation (GEE) models and will be adjusted for possible confounding factors and baseline values of depressive symptoms, quality of life or each biochemical parameter, respectively.

Subgroup and sensitivity analyses will be done under different assumptions. To assess a possible interaction between the intervention and some variables (e.g., age, sex or the presence of non-communicable diseases), product terms will be introduced in the multivariable models. *P* values for the interaction will be calculated using the log-likelihood ratio test.

Multiple imputation will be employed for handling missing data [30, 31].

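### Adjustment of the recurrence comparison for residual depression depends on observed imbalance and does not name the pre-randomisation Beck score; it should be fixed in advance, for a modest gain in power

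*Protocol article*

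**What the plan says.** All references are to the Protocol article.

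- **Recurrence test** (Sample size and data analyses): "Log Rank analysis will be used to assess the effect of the intervention on the risk of depression recurrence". No covariates or strata are stated for it.
- **When adjustment enters** (same section): Cox models are brought in if the arms are found to differ at baseline. The long covariate list ends with "presence, number, and time since last of depressive symptoms/episodes, and family history of mental disorders". Neither the Beck score nor the type of remission is named.
- **What is known before allocation** (Patient recruitment): at the eligibility interview "participants also self-complete the Beck Depression Inventory to assess depressive symptoms". Under Randomization, assignment follows once the specialists have entered the participant's data. Table 1 excludes scores above 18, so scores up to 18 are admitted. Under Inclusion criteria, participants "are in a stage of total or partial remission within the last six months".
- **Randomisation strata** (Randomization): sex, age group and centre. No measure of depression is among them.
- **Symptom analysis** (Sample size and data analyses): the GEE models are adjusted, without any condition on imbalance, for "baseline values of depressive symptoms, quality of life or each biochemical parameter".

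**The concern.** Residual depression at entry may well predict recurrence, and a continuous measure of it exists for everyone before allocation. Yet the recurrence analysis uses residual depression only if an imbalance is noticed, and then through a loosely worded item (presence of symptoms) rather than the score itself.

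Two things are at stake. The first is efficiency: in a time-to-event analysis, always adjusting for a prognostic baseline variable raises the power of the treatment test. The second is the decision rule: whether the reported hazard ratio is adjusted depends on what the baseline table shows. Covariates are better chosen in advance because they are prognostic than afterwards because they happen to differ. Recurrence and residual symptoms stand together in the primary objective, but only the symptom analysis always uses its baseline value.

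**Working it through.** **Inputs from the article.** 250 per group with 5% attrition, so 250 × 0.95 = 237.5 evaluable, taken as 237 in the simulations. On the risks: "The assumed recurrence rate was 50% for the control group and 35% for the group assigned to the Mediterranean diet". The target is 80% power over two years.

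**Assumptions.** Two-sided 5%, because the article gives no significance level for the sample size but reports 95% intervals. The Beck score is treated as a standard normal covariate with an assumed hazard ratio per SD; the article gives none, so a range is shown.

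**1. The plan's own figure.** For two proportions with mean 0.425:

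n = [1.96·√(2 × 0.425 × 0.575) + 0.842·√(0.50 × 0.50 + 0.35 × 0.65)]² / 0.15² ≈ 170 per arm, and 170/0.95 ≈ 179.

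With continuity correction this is 183, then 193. The stated 250 is not reproduced at 80% power. That is a separate matter; here it means only that the starting power is above target.

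**2. Power of the planned log-rank test.** The implied hazard ratio is ln 0.65 / ln 0.50 = 0.621, with |ln 0.621| = 0.476. Expected events are 475 × 0.425 ≈ 202. By Schoenfeld's formula, z = (√202 / 2) × 0.476 − 1.96 ≈ 1.42, which gives power of about 92%. The two-proportion formula gives 91%.

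**3. Power with adjustment.** Simulated trials used exponential times, censoring at two years, 237 per arm, and overall risks held at the plan's 50% and 35%. A Cox model with arm only was compared with arm plus baseline score.

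| Assumed HR per SD | Without score | With score | Gain (points) |
|---|---|---|---|
| 1.3 | about 92% | about 93% | about 1 |
| 1.5 | about 92.5% | about 94% | about 1.5 |
| 1.8 | about 91% | about 95% | about 4 |

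A separate run with 500 trials per setting gave 91.8% and 91.8% at an HR per SD of 1.0, 89.6% and 90.6% at 1.25, 92.8% and 95.0% at 1.5, and 92.2% and 97.2% at 2.0. Each figure there has a Monte Carlo error of about 1.2 points. The gain is nil if the score is not prognostic and a few points if it is.

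**4. A smaller effect.** At an assumed hazard ratio of 0.68 given the score, which is not in the documents, power without and with adjustment was 77.6% and 79.2%, 75.8% and 79.2%, and 72.5% and 80.3% for HR per SD of 1.3, 1.5 and 1.8. The gains are 1.6, 3.4 and 7.8 points. These runs hold the conditional hazard ratio fixed, so the difference between the arms' overall risks shrinks as the score becomes more prognostic. Only the within-pair gains should be read from them, not the fall in the unadjusted column.

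**5. Chance imbalance.** A 1.96-SD imbalance is 1.96 × √(2/237) = 0.18 SD of the score. The unadjusted hazard ratio would move by a factor of exp(0.18 × ln h), that is 1.05, 1.08 or 1.11 for h = 1.3, 1.5 or 1.8. This is the edge of what chance produces in 5% of trials, not a typical value.

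**The case against.** A reader might infer that the recurrence analysis never uses residual depression. The article does not support that. Every participant has had an episode, so presence can be informative in the Cox list only for symptoms, and presence of symptoms is naturally read as residual depression. Naming the instrument and its scale is also detail that a condensed article may leave to the full protocol or SAP. What stands is that the article itself makes adjustment conditional on an observed difference.

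A reader might also infer that a chance difference in residual depression passes straight into the result or biases it. It does not: the log-rank test is valid under randomisation, its type I error already allows for such imbalance, and the conditional Cox model is the plan's stated response to it.

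Nor does the planned test lose power against the plan's own assumptions. With the overall risks held at 50% and 35%, its power stays near 91 to 92% however prognostic the score is. Adjustment is an improvement on an adequate test, not the repair of a deficient one. The hazard ratio nearer to 1 without adjustment is a different (marginal) quantity, not an error.

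The contrast with the GEE models is not a contradiction either, since a change model naturally conditions on its own baseline while time to recurrence has none. Finally, no section shown says that total versus partial remission is stored as a variable, and the contents of Table 3 are not visible. These objections narrow the point but leave the conditional trigger in place.

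**Conclusion.** The point holds in a limited form. Adjustment for residual depression in the recurrence comparison is triggered by observed imbalance and vaguely worded, when it could be fixed in advance using a score that participants already complete before randomisation. The consequence is some lost efficiency and a data-driven choice of model; there is no bias and no invalid test. At the plan's own risks the gain is about 0 to 4 points on a power of about 91 to 92%, and somewhat more if the true effect is smaller. These figures rest on an assumed HR of 1.3 to 1.8 per SD of Beck score, two-sided 5%, exponential times and a normally distributed score. Real scores are cut off at 18, and remission type was not simulated.

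**What to change.** State in the analysis section that the primary recurrence hazard ratio, its 95% confidence interval and its test come from a Cox model that always includes the continuous pre-randomisation Beck score, and total or partial remission if that is recorded, whatever baseline differences are seen. Keep the log-rank test as a supportive analysis.

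The Beck score needs no new data, and the change takes about one sentence. The downside is that the hazard ratio becomes conditional on baseline severity. In the simulations with risks of 50% and 35%, the conditional hazard ratio was 0.608 at an HR per SD of 1.5, against 0.621 unadjusted, so the report should say which of the two it gives.

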## Materials and methods

### Design

Multicenter, two-arm, parallel-group clinical trial. One group of patients (arm 1) is assigned to a Mediterranean diet supplemented with extra-virgin olive oil and the second group (control) (arm 2) has no nutritional intervention. The participants are recruited from four centers across Spain: Hospital [name] (Las Palmas de Gran Canaria), Clínica Universidad de Navarra (Pamplona), Hospital Universitario (Vitoria), and Clínica [name] (Madrid). The intervention period lasted two years.

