### Randomization

Study participants are randomly assigned to one of two groups (Mediterranean diet or control) once their data are included in a centralized computer system by the specialists. Various stratification factors are considered for the randomization, sex, age group (< 65 years or ≥ 65 years) and recruitment center. At baseline, psychiatrists and clinical psychologists are blinded to the allocation of the participants, following the CONSORT guidelines for randomized trials to prevent selection biases.

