## Discussion

Recent studies have assessed the role of the Mediterranean diet in patients with depressive disorders. Jacka et al. reported improvements in depressive symptoms in a sample of 56 depressive patients after 12 weeks of a dietary intervention with a Mediterranean diet in comparison to a social intervention [13]. Similarly, Parletta et al. observed reduced depression and higher quality of life among participants with higher MedDiet scorings in a clinical trial of 95 depressive patients based on the intervention with a Mediterranean diet supplemented with fish [14]. However, these small trials did not evaluate the long-term effect on depression of the Mediterranean diet. Moreover, the aim of the trials was to assess the role of the Mediterranean diet in the treatment of depression and not on its prevention.

The MooDFOOD prevention trial examines the feasibility and effectiveness of two different nutritional strategies (multi-nutrient supplementation and food-related behavioral change therapy). However, it does not examine the effect of a Mediterranean diet intervention in preventing depression in subjects with overweight and have elevated depressive symptoms, but with no current -or in the last six months- criteria for an episode of major depressive disorder [32].

Therefore, to the best of our knowledge, the PREDI-DEP clinical trial is the first randomized clinical trial designed to assess the role of a MDP in the prevention of recurrent depression. Preventing recurrence of depression is one of the priorities in the management of patients with depression, particularly when the number of relapses is high. Whereas the risk of recurrence is approximately 40–60% in patients with a unique depression episode, this risk raises to 90% in patients with three or more previous episodes [33, 34]. Our study provides essential evidence regarding the effectiveness and cost-effectiveness of improving the diet based on a Mediterranean eating pattern for preventing the recurrence of depression and improving the quality of life of patients with previous episodes of depression.

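### The hazard ratio and any use of the randomisation factors depend on an undefined finding of baseline imbalance

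*Protocol article*

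**What the plan says.** Randomization: "Various stratification factors are considered for the randomization, sex, age group" (split at 65 years) and recruitment centre. Under Design, "The participants are recruited from four centers across Spain", so the factors define 4 × 2 × 2 = 16 strata.

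Sample size and data analyses gives the test for recurrence: "Log Rank analysis will be used to assess the effect of the intervention on the risk of depression recurrence". No stratification is stated. The next sentence is conditional: "If distribution differences of baseline characteristics are detected, the Cox proportional-hazards regression models will be used". The purpose given for that model brings in the randomisation factors for the only time in the analysis: "to check by recruitment center, age group and sex, and adjusting for possible confounding factors". A list follows that covers social, clinical, lifestyle, treatment and psychiatric-history variables. The paragraph ends: "Hazard ratios (HR) and 95% confidence intervals (CI) will be calculated considering the control group as reference".

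The text does not say what counts as a detected difference, whether all listed covariates enter or only the imbalanced ones, whether the Cox result replaces or accompanies the log-rank result, or which model supplies the hazard ratio if no difference is detected. By contrast, the GEE analyses of symptoms, quality of life and biochemistry are adjusted for baseline values without any such condition.

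**The concern.** A rule that adjusts only after imbalance has been found chooses covariates by chance imbalance, not by prognostic value. The randomisation factors are balanced by design, so they will rarely set off the trigger, yet they are the factors the analysis should always respect. Number of previous episodes is treated the same way. The Discussion puts recurrence at about 40–60% after a single episode, and "this risk raises to 90% in patients with three or more previous episodes", yet this variable too enters only if the trigger fires.

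The effect estimate is at stake. An adjusted and an unadjusted hazard ratio are different quantities even under perfect balance, because the hazard ratio is not collapsible. The plan therefore leaves open which hazard ratio it is estimating until the baseline table has been seen.

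**Working it through.** **1. Does the hazard ratio depend on the trigger?** Set the sentences in order: an unconditional log-rank test; a Cox model if differences are detected; hazard ratios with confidence intervals. The log-rank test produces no hazard ratio. The only other Cox models in the article compare categories of diet adherence, not the randomised arms. So the only stated source of a hazard ratio for arm 1 versus arm 2 is the triggered model.

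**2. How often would the trigger fire by chance?** Counting antidepressant type, dose and use as one item, and presence, number and recency of episodes as one item, the list has 12 covariates. Counted separately, it has 16. The article gives no threshold, so I assume independent tests at level a:

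P(at least one) = 1 − (1 − a)^k

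- k = 12, a = 0.05: 1 − 0.95^12 = 0.46
- k = 16, a = 0.05: 1 − 0.95^16 = 0.56
- k = 16, a = 0.10: 1 − 0.90^16 = 0.81

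This is the chance that the model is invoked, not the chance of a wrong conclusion.

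**3. What does leaving out the strata cost?** The plan states "250 people per group were required (assuming an attrition of 5"%), with 80% power for 50% versus 35%. Alpha is not stated. At a two-sided 5% level:

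n = [1.96·√(2 × 0.425 × 0.575) + 0.842·√(0.5 × 0.5 + 0.35 × 0.65)]² / 0.15² = 170 per arm

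Allowing for attrition, 170/0.95 gives 179; with a continuity correction the figures are 183 and 193. These do not reproduce 250, but nothing below depends on that. I take the plan's size after attrition: 250 × 0.95 = 237.5, so 237 per arm and 474 in all.

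The implied hazard ratio is ln(0.65)/ln(0.50) = 0.621.

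Simulation assumptions, none of which is in the article: exponential times, four centres of equal expected size, 20% aged 65 or over, 65% women, balanced allocation within strata, and 4,000 runs per cell. Each stratification factor is given the stated log hazard ratio per standard deviation.

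| Log HR per SD | Type I error, unstratified | Type I error, stratified | Power, unstratified | Power, stratified |
|---|---|---|---|---|
| 0 | 5.2% | 5.4% | 92.2% | 91.8% |
| 0.3 | 3.7% | 5.2% | 89.9% | 91.9% |
| 0.5 | 1.9% | 4.4% | 84.5% | 92.2% |

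The power difference from stratifying is 91.8 − 92.2 = −0.4, 91.9 − 89.9 = +2.0 and 92.2 − 84.5 = +7.7 points. Simulation error is about √(0.05 × 0.95/4,000) = 0.3 points for type I error and √(0.92 × 0.08/4,000) = 0.4 points for power.

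**4. Does the switch itself inflate type I error?** A second simulation used 474 participants, 16 independent covariates of which 6 were prognostic, and 5,000 runs. It moved mechanically to the adjusted Cox model whenever any baseline p was below 0.05. Type I error was 5.6%, 4.7% and 4.8% at log hazard ratios of 0, 0.15 and 0.3 per standard deviation. Taking the smaller p-value after a trigger gave about 6%.

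**The case against.** The strongest reply is that the log-rank test is stated without condition and the Cox model is introduced as a check. A reader might infer that chance imbalance decides the primary p-value. The article does not say so: nothing in it lets Cox replace the log-rank test. That part of the reply stands, and the point is confined to the hazard ratio and the adjusted result.

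The absence of stratification is also silence rather than a statement, and a fuller plan may settle it. That too is fair for the log-rank test taken alone. It does not cover the conditional sentence, which is a stated rule and not an omitted detail.

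Three other inferences are tempting and unsupported:

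- **False positives.** A reader might suppose that the rule inflates them. The simulations show a conservative unstratified test and a mechanical switch close to 5%. The article also has a blinded researcher do the analysis, which limits deliberate selection, though not dependence on chance.
- **Post-randomisation covariates.** Several listed variables are re-collected yearly, but the sentence concerns baseline characteristics, and time-varying exposures are assigned to separate marginal structural models.
- **Episode count as the dominant prognostic factor.** The article does not call it that. Its 90% refers to three or more episodes, whereas its one-to-three enrolment mix divides at two or more.

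**Conclusion.** The point holds as a fault of specification. The article makes the randomised hazard ratio, its adjustment, and any use of the randomisation factors depend on an undefined detection of baseline differences. Under the assumed 5% independent tests, that trigger is close to a coin toss (46–56%). It does not endanger type I error. The cost of omitting the strata is negligible if they are weakly prognostic, about 2 points of power at a log hazard ratio of 0.3 per standard deviation, and nearly 8 points at 0.5. Those effect sizes are assumptions; the article gives no data on how prognostic the strata are.

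One qualification concerns the word chance. Under Baseline information, the dieticians' first call discloses the arm, and the dieticians also complete the general, activity and food-frequency questionnaires. The order is not shown. Differences in those items could therefore partly reflect knowledge of the arm, which makes them a still poorer trigger.

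**What to change.** Delete the condition. Prespecify one primary analysis in which the test of the arm effect and the hazard ratio with its 95% confidence interval come from the same model, used whatever the baseline table shows. An example is a Cox model stratified by centre and adjusted for sex, age group, number of previous episodes and baseline Beck score. All of these are available from the eligibility assessment or randomisation. State the coding of episode number in advance. Stratifying by centre alone, with sex and age group as covariates, avoids 16 strata averaging 474/16 ≈ 30 participants, and it should be settled now and not left to depend on observed counts.

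Move the long covariate list to a sensitivity analysis, restricted to baseline values. Note there that the article does not show the dietician-collected items to precede disclosure of the arm.

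The cost is wording only, with no new data and no larger sample. The change should be made before anyone sees outcomes by arm, since a later choice could not be defended as prespecified.
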